### Objectives {7}

Aim 1: Implement the intervention in 12 high-volume health facilities: Guided by the Consolidated Framework for Implementation Research [9, 10], we will engage stakeholders and assess facility organizational readiness prior to implementation. No PPFP activities are currently taking place in these facilities. We will implement the PPFP intervention in a clinic-randomized stepped-wedge design. We expect to deliver PPFP promotional counseling to over 21,000 pregnant or postpartum women/couples.

Aim 2: Evaluate intervention effectiveness and implementation: The RE-AIM framework [11] will guide the outcome evaluation. We hypothesize that the intervention will significantly increase the number of stakeholders engaged, PPFP providers and promoters, couples/clients receiving information about PPFP, and LARC uptake comparing intervention versus standard of care. We expect PPFP client satisfaction will be high, and side effects will be rare. The independent effectiveness of each demand creation strategy on LARC uptake will be estimated. We assess the measures of intervention adoption, implementation, and maintenance at the patient, provider, and stakeholder levels to assess the intervention sustainability.

Aim 3: Evaluate intervention cost-effectiveness and cost-utility: We employ standard methods [12, 13] to estimate the costs and incremental cost-effectiveness and cost-utility of the intervention relative to the standard of care from the societal perspective. The cost-effectiveness of each demand creation strategy will be estimated. We hypothesize that the intervention will be cost-saving relative to the standard of care. A costed implementation plan will be developed to guide Rwandan MOH decision-making for the nationwide roll-out of PPFP services.

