#### In-depth interviews

To explore the barriers to intervention implementation, we will conduct one-on-one in-depth interviews with *n* = 12 facility directors, *n* = 24 nurses in charge of L&D and family planning (2/facility), *n* = 24 CHW (2/facility), and *n* = 5 MOH stakeholders. CFIR provides guidance for qualitative semi-structured interview constructs [10]. Interviews will take 30 min, and participants will be compensated. Interview guides will be translated into the primary local language (Kinyarwanda) and pre-tested. Interviews will be anonymized and conducted by the research staff experienced in leading in-depth interviews.

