### Sample size {14}

Table 4 shows the expected number of participants included in each study activity. We assume that the proposed sample sizes shown below for in-depth interviews will allow us to reach saturation. Based on facility volume and preliminary findings, we conservatively expect to deliver PPFP promotions to 12,714 in the 12 intervention facilities (18% of reproductive age women in the catchment area) and 21,383 women/couples total across the 17 facilities (12 intervention plus 5 training facilities).

**Table 4 Tab4:** Expected number of participants included for each study activity

Specific aim	Activity	Total participants
Aim 1	In-depth interviews	12 facility directors 24 nurses in-charge of L&D and family planning 24 CHWs 5 MOH stakeholders
Aim 2	Intervention trainings	98 government facility PPFP promoters 68 community health worker promoters 78 government facility PPFP providers (70 certified) 36 Happy Client promoters
	Intervention recipients	We expect to deliver PPFP promotions to *n* = 12,714 women/couples
	In-depth interviews	25 women/couples 25 providers 25 stakeholders

We assume based on our pilot that promotions will reach 75% of pregnant women in health centers. Also extrapolating from our pilot data, we also expect to insert 3687 PPIUDs and 1399 PP implants in the 12 intervention facilities (6201 PPIUDs and 2352 PP implants total across the 17 facilities) (Table 5). Given the facility volume and previous experience, PPFP service delivery to this number of women is highly feasible. Sample size and power calculations account for intra-cluster correlation (ICC) which considers the between-cluster correlation, within-cluster correlation, and repeated measures. We assume pooled between- and within-cluster ICCs and a homogeneous intervention effect over time. We have > 80% power to detect all differences in the expected proportions shown in Table 5 comparing PPFP intervention to control.

**Table 5 Tab5:** Expected deliverables during the study time period, *n* = 12 intervention facilities. Power to detect the differences between standard of care control and intervention: > 80%

Stakeholders	Control^**a**^			PPFP intervention		
	***N*** events	Denominator	Expected %	***N*** events	Denominator	Expected %^**b**^
Clinic directors engaged	2	12	17%	12	12	100%

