**Clients delivering at implementation facilities**						
Promotions to pregnant or postpartum women/couples	268	17,870	2%	12,714	17,870	71%
PPIUD insertions	20	268	7%	3687	12,714	29%
PP implant insertions	14	268	5%	1399	12,714	10%

^a^Data from *n* = 12 government clinic logbooks, 2018

^b^Estimated from the pilot study [5]

^c^In ANC, L&D, FP, and IV

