## Statistical methods

### Statistical methods for primary and secondary outcomes {20a}

#### Reach and adoption

We will tabulate, overall and by facility, the number of stakeholders engaged, providers trained, promoters trained, providers certified and pre/post-training evaluation scores, and clients who received one-on-one counseling. We hypothesize increases comparing intervention versus standard of care in stakeholders engaged, providers trained to promote and provide PPFP, and couples/clients receiving information about PPFP (Table 5). We expect 90% of trainees will receive certification to promote and provide PPFP.

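### The power and hypothesis for clinic directors engaged rest on a 2018 control value (2/12) that the trial's own control periods are unlikely to show, because Aim 1 reaches all 12 directors before any clinic crosses over

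*Protocol article*

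**What the plan says.** **Power.** Sample size {14}: "We have > 80% power to detect all differences in the expected proportions shown in Table 5 comparing PPFP intervention to control". The title of Table 5 repeats the claim for standard of care against intervention. Its first row, "Clinic directors engaged", reads 2/12 (17%) under control and 12/12 (100%) under intervention. The footnote to the control column gives its source: "Data from *n* = 12 government clinic logbooks, 2018". Table 1 marks stakeholders engaged and staff trained as outcomes used in the power analysis.

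**Hypothesis.** The Abstract and Objectives {7} (Aim 2) expect a significant increase in stakeholders engaged compared with standard of care. Statistical methods {20a}, Reach and adoption, repeats this with reference to Table 5: "We hypothesize increases comparing intervention versus standard of care in stakeholders engaged, providers trained to promote and provide PPFP".

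**Comparator.** Trial design {8} and the section on choice of comparators {6b} make each facility its own standard-of-care control.

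**Timing.** For Aim 1, Objectives {7} says: "we will engage stakeholders and assess facility organizational readiness prior to implementation". The In-depth interviews section adds: "we will conduct one-on-one in-depth interviews with *n* = 12 facility directors". The consent section {26a} places these interviews in year 1, and Table 2 places them in the second half of that year. Table 2 opens the stepped wedge in the first half of year 2. The stakeholder-level part of Maintenance lists clinic directors among the stakeholders. The Stakeholder engagement section describes one further activity, quarterly presentations to the national family planning working group.

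**The concern.** A controlled contrast needs a comparator that could show the control value. Here the comparator is a clinic's own period before crossover, but the study team contacts the director of every clinic before the first of those periods begins. A proportion taken from 2018, before that contact, does not describe what those periods will show.

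If directors contacted in Aim 1 count as engaged, the row has little or no room to rise at crossover. The power statement and the expected significant increase would then describe a change from 2018 to the trial, which is an unrandomised before-and-after comparison. A reader who sees this row under a blanket power claim for a randomised design would credit the design with something it cannot deliver for this outcome.

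**Working it through.** **1. Inputs.** From Table 5: control 2/12, intervention 12/12. There is one director per clinic, so the intra-cluster correlation plays no part in this row. Table 5 states no alpha; I assume 0.05, two-sided.

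**2. Reproducing the plan's figure.** With 12 against 12, the exact Fisher test of 2/12 versus 12/12 gives p = 0.00007. When the intervention arm is 12/12, Fisher's test rejects if at most 7 control directors are engaged (7/12 versus 12/12, p = 0.037; 8/12 versus 12/12, p = 0.093). Power is therefore P(X ≤ 7) for X ~ Binomial(12, c/12), where c is the number of directors expected to be engaged under control. At c = 2 this is 99.98%. The stated power above 80% follows from the plan's own inputs.

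**3. Changing only the control value.**

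| Engaged under control (c of 12) | Fisher p for c/12 vs 12/12 | Exact Fisher power |
|---|---|---|
| 2 | 0.00007 | 99.98% |
| 4 | 0.0013 | 98% |
| 6 | 0.014 | 81% |
| 7 | 0.037 | 61% |
| 8 | 0.093 | 37% |
| 10 | 0.48 | 4% |
| 12 | 1 | 0 |

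The claim fails once 7 of the 12 are engaged before crossover. At 12 of 12 the difference is zero.

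**4. Paired version.** The same 12 clinics supply both values, so an exact McNemar test is arguably closer to the design. With everyone engaged after crossover, it rejects when at least 6 directors change (2 × 0.5⁶ = 0.031; with 5 changes, 2 × 0.5⁵ = 0.0625). Power is P(D ≥ 6) for D ~ Binomial(12, (12 − c)/12): 99.9% at c = 2, 81% at c = 5 and 61% at c = 6. The margin is one director smaller than with Fisher's test.

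**5. Which value of c the schedule implies.** Aim 1 plans interviews with 12 facility directors, which is all of them, in the second half of year 1. The first crossover cannot come before the first half of year 2. The working group meetings are national and are not tied to any clinic's crossover. No described activity engages a director specifically when that clinic crosses over. If Aim 1 contact counts, c is at or near 12.

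**6. Training and certification rows, for contrast.** Nurses trained (7/215 vs 98/215), CHWs trained (0/313 vs 68/313), providers trained (7/162 vs 78/162) and providers certified (0/162 vs 70/162) have power near 100% without clustering. The plan gives no intra-cluster correlation, so I applied a parallel-arm design effect, 1 + (m − 1) × ICC with m = n/12, over assumed values. Up to an ICC of 0.2, power is at least 95.6% in all four rows. At an extreme 0.5 it is 94%, 67%, 94% and 97% in the order listed. Clinics not yet crossed over supply a concurrent comparator for these rows, so the problem with the directors row does not carry over. The intervention numerators 98, 68, 78 and 70 are, however, the same numbers that Table 4 gives for intervention trainings, so these rows record how far the intervention was delivered.

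**The case against.** **Engagement is undefined.** The Aim 1 interviews are meant to explore barriers to implementation. Engagement is counted from an advocacy and training log, and nothing says that an interview is entered there. The step layout in Table 3 is also not shown. This stands: that Aim 1 contact counts as engagement is inferred, not stated. The inference is well supported, because Aim 1 itself says stakeholders are engaged before implementation and the protocol lists clinic directors as stakeholders.

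**Only tabulation is planned.** A reader might infer that the trial will test its results against 2018. The documents do not support that: the 2018 figures are planning values, and the Reach and adoption paragraph names no test or model. This limits the point to the power claim and the hypothesis. Both still promise an inference for this row.

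**Training rows.** A reader might extend the point to say that the training and certification rows lack a valid comparator or are significant by construction. That goes too far. Clinics awaiting crossover are a concurrent comparator, the intervention percentages are described as pilot estimates, and certification depends on trainees passing a test and completing supervised insertions. These counts are also declared RE-AIM outcomes in a hybrid effectiveness-implementation study. Nor would it be consistent to strike them as study inputs while keeping promotions, which the intervention also delivers. What remains is a matter of labelling.

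**Conclusion.** The point holds for the directors row. Its control value of 2/12 predates study contact that the schedule gives to all 12 directors before the wedge opens, so the power above 80% and the expected significant increase are not properties of this design for that outcome. The arithmetic is sound on the 2018 input; the input does not represent the comparator.

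In size, exact Fisher power drops from 99.98% at 2/12 to 61% at 7/12 and to 0 at 12/12. This rests on three assumptions: Aim 1 contact counts as engagement, engagement persists as a state once it has occurred, and alpha is 0.05 two-sided. If at most 6 directors were engaged under control, the power claim would survive on Fisher's test (at most 5 on the paired test).

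For the four training and certification rows, the power claim stands over plausible clustering, apart from CHWs at an extreme assumed correlation. They need only be labelled as delivery of the intervention. The planned model for postpartum LARC uptake is untouched.

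**What to change.** Choose one of two wordings for the directors row.

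- **Descriptive.** Remove it from the blanket power statement and from the hypothesised significant increase in stakeholders engaged. Report directors engaged as delivery against the target of 12/12, with the 2018 value of 2/12 as background, and state that Aim 1 contact preceded crossover in all 12 clinics.
- **Comparative.** Define engagement as a logged, clinic-specific event that can occur only after that clinic crosses over, and say that Aim 1 interviews and working group meetings do not count. Even then, the result shows that the step was delivered.

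Keep the four training and certification rows as reach and adoption measures, with clinics not yet crossed over as comparator, and add a sentence that they document delivery of the intervention and are not evidence of its effectiveness.

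The cost is wording in Objectives {7}, Sample size {14}, Table 5 and the Reach and adoption paragraph. Design, data collection and the uptake analysis stay as they are, except that the comparative option needs a dated engagement entry in the existing log.

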**Promotions**						
Nurses^b^ trained to promote PPFP	7	215	3%	98	215	46%
CHWs trained to promote PPFP	0	313	0%	68	313	22%
**Providers at implementation facilities**						
Providers trained to provide PPFP	7	162	4%	78	162	48%
Providers certified to provide PPFP	0	162	0%	70	162	43%
**Clients delivering at implementation facilities**						
Promotions to pregnant or postpartum women/couples	268	17,870	2%	12,714	17,870	71%
PPIUD insertions	20	268	7%	3687	12,714	29%
PP implant insertions	14	268	5%	1399	12,714	10%

^a^Data from *n* = 12 government clinic logbooks, 2018

^b^Estimated from the pilot study [5]

^c^In ANC, L&D, FP, and IV

### Recruitment {15}

Aim 1/2: In-depth interviews: Participants will be recruited by random sample, purposively distributed across the intervention facilities.

Aim 2: Implement intervention services in a clinic-randomized stepped-wedge trial: All eligible nurse/midwives and CHW at the selected facilities will be recruited as PPFP providers and/or promoters. Happy Clients will be recruited by convenience, distributed across the intervention facilities. Women receiving intervention services will not be recruited; all women receiving care at one of the selected facilities during the intervention time period will be offered the intervention.

## Assignment of interventions: allocation

### Sequence generation {16a}

Each clinic will be randomized using the SAS random number generator (SAS Institute v9.4, Cary, NC). The allocation ratio will be 1:1. There will be no stratification or blocking. The facilities are all of similar, high-volume, and have similar client volume and staffing-to-patient ratios.

### Concealment mechanism {16b}

The allocation sequence will not be visible to the trial staff conducting randomization so that the assignment will be unknown to staff until each numbered, security-type envelope is opened.

### Implementation {16c}

The allocation sequence will be generated by trained study staff. Clinic intervention assignment will be conducted by trained study staff.

## Assignment of interventions: blinding

### Who will be blinded {17a}

There is no blinding in this study. Providers and clients in intervention facilities will know that the intervention is being implemented in that facility.

### Procedure for unblinding if needed {17b}

The design is open-label, so unblinding will not occur.

## Data collection and management

### Plans for assessment and collection of outcomes {18a}

The number of stakeholders engaged and providers trained and certified will be recorded in an Advocacy and Training logbook. CHW counseling activities will be measured on referral slips which will record if a male partner was present. Women/couples receiving one-on-one PPFP counseling will have their method of interest, whether a male partner was present, household income, and estimated date of delivery recorded in a PPFP logbook, developed by the study team during the pilot and maintained by government clinic staff. The PPFP logbook will also record PPFP uptake and, among PP LARC users, provider perception of ease of insertion, client anxiety during insertion, and client pain during insertion (scales of 1–10). During follow-up visits, the PPFP logbook will record PPFP side effects and method failures. Facility information, client’s age, and parity will be abstracted from government Family Planning logbooks.

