#### PPFP demand creation training

We will train the government clinic staff in family planning, ANC, L&D, and IV to promote PPFP at the selected facilities. Trainings will comprise a 3-h-long didactic session led by the trained research staff followed by two supervised counseling sessions. CHWs from the health centers in charge of pregnant women and newborn health will receive a 1-day training on the PPFP flipchart. If interested in PPFP, women will be referred to the facility by their CHW. We will develop training materials to coach Happy Clients to discuss their own experiences with PPFP and address common concerns (as identified in our formative work and also addressed in the promotional flipchart). Happy Clients will be distributed equally across intervention facilities, affiliated with only one facility, and will be partnered with trained PPFP counselors. Finally, we will create an educational video in which a nurse counselor describes the PPFP flipchart information, visually shows each PPFP option, and men and Happy Clients give brief testimonies as to their experiences with different PPFP methods. Videos providing PPFP information will be shown in the ANC, L&D, and IV waiting areas in intervention facilities.

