#### Effectiveness

##### Primary analyses

We will tabulate, by facility, a total number of all PPFP methods provided and the proportion of PPFP uptake among women who delivered at one of our facilities (overall and by method type). PP LARC uptake (by method type) will be evaluated using logistic regression and general estimating equation methods to account for the clinic-randomized design. The main predictor will be the intervention versus the control arm. For example, the following generalized linear mixed model will compute the adjusted odds ratio for taking up a PP implant: *Y*_*ijl*_ = *β*0 + *β*1 × (intervention_*ij*_) + *β*2 × (covariates_*ij*_) + *β*3 × (intervention_*ij*_ × covariates_*ij*_) + *β4*_*j*_ + *u*_*i*_ + *ε*, where *i* = clusters*, j* = time periods, *l* = individuals, *β*1 = fixed effect for intervention, *β*2 = fixed effects for covariates, *β*3 = fixed effects for interactions, *β*4_*j*_ = fixed effect for time, *u*_*i*_ = random effect for ICC, and *ε*_*ijl*_ = random residual. Covariates assessed as potential confounders will include facility volume, service volume-to-staffing ratio, and number of promotions received. Outcomes will be reported as adjusted odds ratios with 95% confidence intervals. We hypothesize that the intervention will significantly increase PP LARC uptake by comparing intervention versus control. We will also assess the independent effect of each promotional strategy on PP LARC uptake. Every promotion will be recorded and we will estimate the independent effect of receiving CHW counseling, video-based promotions, or Happy Client promotions (treating each strategy as an independent, dichotomous exposure of interest) on PPFP uptake using adjusted multivariate regression modeling with general estimating equations methods.

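### The only described record of community health worker (CHW) counselling is a referral slip, and referral depends on interest, so the planned CHW effect is open to upward bias

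*Protocol article*

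**What the plan says.** Four statements in the protocol article bear on this.

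- Measurement (Plans for assessment and collection of outcomes {18a}): "CHW counseling activities will be measured on referral slips which will record if a male partner was present". No other record of CHW counselling is described.
- Referral rule (PPFP demand creation training): "If interested in PPFP, women will be referred to the facility by their CHW".
- Analysis (Effectiveness, Primary analyses): "Every promotion will be recorded and we will estimate the independent effect of receiving CHW counseling, video-based promotions, or Happy Client promotions". Each strategy is coded as present or absent ("treating each strategy as an independent, dichotomous exposure of interest") in an adjusted regression with generalised estimating equations (GEE).
- Covariates (same section, given with the main model): "Covariates assessed as potential confounders will include facility volume, service volume-to-staffing ratio, and number of promotions received". None of these measures a woman's interest before or at the CHW contact.

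For the video, the training section says "Videos providing PPFP information will be shown in the ANC, L&D, and IV waiting areas in intervention facilities". The logbook fields described at counselling are for women counselled individually: "Women/couples receiving one-on-one PPFP counseling will have their method of interest, whether a male partner was present, household income, and estimated date of delivery".

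**The concern.** The measurement rule, the referral rule and the estimand do not fit together as stated. The analysis needs to know who was counselled by a CHW. The instrument named for this is a form whose purpose is referral, and referral depends on the woman wanting postpartum family planning. If the slip is filled in only at referral, exposure means counselled and interested, and a counselled woman who was not interested joins the unexposed group. Exposure is then defined partly by a precursor of the outcome. GEE deals with clustering by facility, not with this misclassification.

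The estimate answers a stated question. The Background asks whether CHW promotion increases effectiveness and which demand creation strategies are most cost-effective. Aim 2 promises the independent effectiveness of each strategy, and Aim 3 its cost-effectiveness. An inflated CHW estimate would distort the comparison between strategies.

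**Working it through.** The protocol states no effect size, sample size or power for the individual strategies, so there is no figure of its own to reproduce. The check asks what odds ratio the slip coding returns when CHW counselling has no effect at all.

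**Inputs from the document (Table 5)**
- Expected insertions among 12,714 women receiving promotions: 3687 IUDs and 1399 implants. Overall uptake U = (3687 + 1399)/12,714 = 5086/12,714 = 40.0%. This treats each insertion as a different woman.
- Share of CHWs trained: 68/313 = 22%. It is borrowed as one illustrative value for the share of women counselled by a CHW, which the protocol does not give.

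**Assumed inputs (not in the document)**
- q, share of women interested: 0.4 to 0.8
- R, ratio of uptake in interested to uptake in uninterested women: 1.5 to 4
- c, share counselled by a CHW, independent of interest: 0.1 to 0.5
- a slip exists only if the woman was counselled and interested

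**Formulas under no CHW effect**
- Uptake if not interested: u0 = U/(qR + 1 − q). Uptake if interested: u1 = R·u0.
- Share with a slip: s = c·q. Uptake with a slip: u1.
- Uptake without a slip: p = (U − s·u1)/(1 − s).
- Slip odds ratio = [u1/(1 − u1)] / [p/(1 − p)].

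**Direction.** The no-slip group mixes all uninterested women with the interested women no CHW reached. Its uptake therefore lies between u0 and u1, and the odds ratio exceeds 1 whenever R > 1. With R = 1 it is 1.00.

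**Illustrative case (q = 0.6, R = 2, c = 0.22)**
- u0 = 0.40/(1.2 + 0.4) = 0.25; u1 = 0.50
- s = 0.22 × 0.6 = 0.132
- p = (0.40 − 0.132 × 0.50)/(1 − 0.132) = 0.334/0.868 = 0.385
- Odds ratio = 1.00/(0.385/0.615) = 1.60

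**Ends of the assumed range**

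| q | R | c | u1 | p | Odds ratio |
|---|---|---|---|---|---|
| 0.8 | 1.5 | 0.1 | 0.429 | 0.398 | 1.14 |
| 0.6 | 2 | 0.22 | 0.500 | 0.385 | 1.60 |
| 0.4 | 4 | 0.5 | 0.727 | 0.318 | 5.72 |

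**Simulation of the illustrative case.** Sixty data sets were generated with 12 facilities, 12,714 women, a facility standard deviation of 0.3 on the logit scale and no CHW effect, and analysed by logistic GEE without covariates. Slip coding gave an odds ratio of 1.60, with p < 0.05 in all runs. Coding every counselled woman as exposed, interested or not, gave 1.01, with p < 0.05 in 3% of runs. The problem is the coding, not the regression method.

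**If counselling itself creates interest.** Suppose 30% are counselled, counselling raises interest from 40% to 60%, and uptake is 60% in interested and 10% in uninterested women (all assumed).
- True uptake: counselled 0.6 × 0.6 + 0.4 × 0.1 = 0.40; not counselled 0.4 × 0.6 + 0.6 × 0.1 = 0.30. True odds ratio (0.40/0.60)/(0.30/0.70) = 1.56.
- Slip coding: with a slip 0.60; without (0.3 × 0.4 × 0.1 + 0.7 × 0.30)/(0.3 × 0.4 + 0.7) = 0.222/0.82 = 0.271. Slip odds ratio (0.60/0.40)/(0.271/0.729) = 4.04.

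A real effect is then overstated, because the counselling failures have been moved to the unexposed group.

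**The case against.** The strongest reply is that the document never says slips are withheld from women who decline. A form meant to measure counselling activity could be completed at every contact, and the Primary analyses section says that all promotions will be recorded. If so, there is no bias. This stands as a limit: that slips reach only interested women is an inference from two sections read together. It does not remove the point, because the one instrument named for CHW contacts is the referral slip, and the general statement about recording does not say how an unreferred contact would be captured.

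A reader might infer more than the text supports:

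- **That slip holders were already interested, or that the CHW effect must come out positive.** Interest may arise from the counselling itself. The bias is upward only if slips follow referral and interest predicts uptake.
- **That no adjustment could help.** In the null model above, the odds ratio among interested women is exactly 1.00, so a good measure of interest would remove the bias. The method-of-interest field is only a partial substitute: it covers women who reach individual counselling and may be recorded after the CHW contact. The covariates listed with the main model may not be the full set for the strategy analyses.
- **That video viewing has no individual record.** This conflicts with the statement that every promotion is recorded. The article names no source for individual viewing of a waiting-area video, but an article may leave such a field to the full protocol.
- **That Happy Client effects cannot be separated from counselling.** Happy Clients are partnered with counsellors, but there are only 36 of them beside 98 facility promoters (Table 4). Counselling with and without one may be comparable.
- **That the national costed plan would be steered by this estimate.** The article does not say that strategy-specific odds ratios feed the plan.

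**Conclusion.** The point holds as a defect in how CHW exposure is measured for the strategy analysis. As described, the measure depends on interest, and if slips follow referral the CHW estimate is biased upward whenever interest predicts uptake. With no true effect and overall uptake at Table 5's 40%, the odds ratio is 1.6 in the illustrative case and about 1.1 to 5.7 over the assumed ranges. Those sizes rest on values of q, R and c that the protocol does not give; the direction rests only on the two conditions just named. The randomised comparison of intervention with control does not use this exposure and is unaffected.

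**What to change.** - Have CHWs record every woman they counsel, referred or not, under the unique code that the Data management section already uses to follow clients from the community. Define CHW exposure from that record. This also reconciles the referral-slip sentence with the statement that every promotion is recorded.
- Report the strategy estimates, which are not randomised, as adjusted associations rather than independent effects.
- For the video, state where individual viewing is recorded, or do not report an individual-level video effect.

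The cost is one extra line per CHW contact and a softer claim for the strategy comparison. The record has to be in place during delivery, because contacts that were never logged cannot be recovered at analysis.
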